### Duration of study

In this study, 300 infants will be recruited. The trial will terminate when the last recruited infant is discharged from hospital, or dies.

Based on a recent study conducted by our group at the Central Hospital of Beira, Mozambique, we consider that we will perform the study in about 14 months (Table 1).

**Table 1 Tab1:** Duration of the study

Time	2 months	3 months	6 months	1 month	2 months
Task	Preparation of the protocol and Case Report Form (CRF), and material (i.e.. thermometer, woolen cap); (completed)	Ethics and Ministerial Committee approval; (completed)	Data collection	Analysis of the data	Preparation of the manuscript
Done	x	x	x (started in January 2016)		

The study will be conducted – simultaneously – at the three participating hospitals.

### Ethical considerations

Written parental consent is necessary before enrollment of the patients in the study. We consider that there will be no risks for either study group (patients treated with or without a woolen cap). Hypothermic as well as hyperthermic episodes will be strictly monitored in both groups.

### Ethics Committee approval

The study was approved by the Ethics Committees for Human Investigation of the three participating hospitals. At the Central Hospital of Beira the study was approved by the Comitè Nacional di Bioetica para a Saude, Ministerio da Saude (REF: 348/CNBS/15: IRB00002657; Maputo, Mozambique; 8 December 2015); at St. Luke Wolisso Hospital the study was approved by the Lacor Hospital Institutional Research and Ethics Committee (REF: LHIREC N.: 016/03/15; Gulu, Uganda; 30 May 2015); at Aber Hospital the study was approved by the Oromia Regional Health Research Ethical Review Committee Bureau (REF: BEFOABTFH 3657/1-8; Addis Ababa, Ethiopia; 24 June 2015).

### Compliance to protocol

Compliance will be defined as full adherence to protocol. Compliance with the protocol will be ensured by some members of the project (DM, TS, SM, WM) who are responsible for local data collection. They will monitor adherence to the study protocol weekly and will input the patients’ data in an Excel data sheet. Double data entry will be performed by two independent members at each center to promote data quality.

### Missing data

Investigators and study staff will be trained on the importance of completion of the study period of enrolled patients. Parents will also be informed about this crucial aspect to reduce dropout, and a local investigator will be available at each site any time that the parents may need further information or clarification during the study period.

### Data Safety and Monitoring Board

Safety measures will include incidence, severity and causality of reported SAEs, represented by changes in occurrence of the expected common neonatal complications and the development of unexpected SAEs. SAE will be defined as unexpected death, apnea not responding to vigorous stimulation, severe hyperthermia (temperature >39 °C) and hypothermia (temperature <35 °C). All SAEs will be followed until complete resolution or until the clinician responsible for the care of the recruited patient considers the event to be chronic or the infant to be stable.

A monitoring board, including an independent assessor (not involved in the study) from the University of Padova and assessors from each participating hospital, will review all the deaths and adverse events. If there is a reasonable suspected causal relationship with the intervention, SAEs will be reported to the Ethics Committee to guarantee the safety of the participants.

An interim analysis will be performed on the primary endpoint and on SAEs from the first 100 enrolled infants. The interim analysis will be performed by the statistician, who is blinded for the treatment allocation and who will report to the PI. The PI will discuss the results of the interim analysis with the monitoring board and the trial will be ended in case of harm. Criteria for stopping for harm include: a statistically significant difference in the primary outcome between the treatment groups; and a reasonable suspected causal relationship between the intervention and SAEs.

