### Blinding

Due to the characteristics of the intervention, neither caregivers nor outcome assessors will be masked to treatment allocation. However, the statistician who will perform data analysis will be blind to treatment allocation. To minimize bias, strict criteria and definitions will be maintained during the trial.

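### The comparative interim result passes through the PI to a board with assessors from the participating hospitals, while up to 200 of 300 infants in an open-label trial are still to be enrolled

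*Protocol article*

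**What the plan says.** The Data Safety and Monitoring Board section sets out the interim look: "An interim analysis will be performed on the primary endpoint and on SAEs from the first 100 enrolled infants". It fixes the first step of the reporting route: "The interim analysis will be performed by the statistician, who is blinded for the treatment allocation and who will report to the PI". It then fixes the second: "The PI will discuss the results of the interim analysis with the monitoring board and the trial will be ended in case of harm". The board is described as "A monitoring board, including an independent assessor (not involved in the study) from the University of Padova and assessors from each participating hospital". One of the listed criteria for stopping for harm is "a statistically significant difference in the primary outcome between the treatment groups".

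The Blinding section states that "neither caregivers nor outcome assessors will be masked to treatment allocation", while "the statistician who will perform data analysis will be blind to treatment allocation". The Sample size section sets the total at 300.

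**The concern.** In an open-label trial, those who run the study and those who work at its sites are normally kept away from by-arm efficacy results until the data are locked. Here the written route does the reverse. The PI is the first recipient, and the monitors hear the result from the PI.

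Two things are at stake.

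- **Conduct of the remaining trial.** The primary outcome is an axillary reading judged against 36.5 and 37.5 °C, taken by staff who know the allocation. Someone who believes that one arm is doing better may, without intending it, treat borderline readings, repeat measurements or supporting care differently by arm. They may also change which infants are put forward. Neither intention-to-treat analysis nor a blinded final analyst can remove such an effect afterwards.
- **Independence of the monitoring.** If the PI stands between the statistician and the board, the PI shapes what the board hears and when it hears it.

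**Working it through.** No formula tests a reporting route, so the check is to read the statements together and then bound how many infants are exposed.

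1. **Is the interim result comparative?** Yes. A between-group difference in the primary outcome is a stopping criterion, so the report must contain that comparison. Stopping for harm also needs the direction of the difference, so someone must at some point know which arm is which.

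2. **Who receives it, and in what order?** Statistician, then PI, then board. The section describes no direct route from statistician to board, and no limit on what the PI or the hospital assessors may see or pass on. The finding rests on the route that is written, not on a missing detail.

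3. **How close is the PI to the data?** The Data collection section expands the abbreviation as the local principal investigator, and the Confidentiality section gives the local PI access to the trial database. Even if the interim paragraph means a single overall PI, that person still runs the trial.

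4. **Who sits on the board?** An assessor from Padova, described as uninvolved, and assessors from each participating hospital, who are not so described. Their stated task is to review deaths and adverse events, but the interim results, including the primary endpoint, are discussed with the board as a whole.

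5. **How many infants are exposed?**
 - The plan's own total reproduces: 150 + 90 + 60 = 300 by hospital, and 150 + 150 = 300 by arm.
 - The interim fraction is 100/300 = 33.3%, leaving 300 − 100 = 200 infants (66.7%). This is the upper bound, reached only if nobody is enrolled between the 100th infant and release of the result.
 - The protocol mentions no recruitment pause. The 100th infant is treated for up to 7 days (Procedure), and data collection lasts 6 months (Table 1). Assuming uniform accrual, 300/6 = 50 infants a month, or about 300/182.5 = 1.64 a day.
 - Assuming 2 to 4 weeks for the interim analysis, the delay is 7 + 14 = 21 to 7 + 28 = 35 days. That is 21 × 1.64 ≈ 35 to 35 × 1.64 ≈ 58 further infants enrolled before release.
 - About 200 − 58 = 142 to 200 − 35 = 165 infants would then be enrolled afterwards, which is 47% to 55% of the total.

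6. **Size of any bias.** The documents contain no input for it. If knowledge shifted the arm difference by d points in all 200 remaining infants, with similar numbers of readings per infant, the final difference would move by d × 200/300, or two thirds of d. With 142 to 165 infants it would move by 0.47d to 0.55d. Nothing in the protocol supplies d.

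**The case against.** The strongest reply is that the statistician is blinded, so the report may show only coded arms, and that the protocol has other protections.

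- **Coding.** The text does not say whether the report is decoded for the PI, so a reader should not take it as stated that the PI sees named arms. But blinding the analyst does not blind the recipient. A harm decision needs direction, and the local PI has access to the database of an unmasked trial. Coding alone is weak protection.
- **Selection.** Allocation is held in opaque, sealed, sequentially numbered envelopes, opened only once the infant is judged eligible. Knowing an interim difference does not reveal the next allocation, so there is no clear route to selection between arms. What remains is a possible change in case mix, because candidacy for kangaroo care is a clinical decision.
- **Measurement and co-care.** Data are to be collected by an observer outside the infants' care, with a specified digital thermometer, and blanket changes are tied to the temperature limits. These measures narrow the room for bias. They do not close it: outcome assessors are unmasked, and the midwives and nurses responsible for care are also trained in temperature measurement and data collection.
- **Hospital assessors.** A reader might infer that they are the people who enrol, treat or measure infants, or that bedside staff will be told the result. The documents say neither. They say only that assessors from those hospitals are on the board with which the results are discussed.
- **The decision.** A reader might also infer that the PI decides whether the trial continues. The text does not assign that decision to the PI. It says that the PI discusses the results with the board and that the trial ends in case of harm.

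**Conclusion.** The point holds as a matter of governance and protection against bias. The protocol itself routes a by-arm primary-outcome comparison through the PI to a board that includes participating-hospital assessors, in a trial where caregivers and outcome assessors are unmasked. That creates an avoidable risk to measurement, co-care and case mix in the infants not yet enrolled.

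The exposure is at most 200 of 300 infants. It is roughly 140 to 165 if recruitment continues at a uniform 50 a month and the interim analysis takes 2 to 4 weeks; both of these are assumptions. It is tempting to treat 200 as the exact number or to attach a percentage-point bias to it. The documents support neither: no pause is described, and no figure for the effect of such knowledge is given. The finding is that bias is possible and easily prevented, not that it will occur.

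**What to change.** Amend the Data Safety and Monitoring Board section as follows, before the 100-infant look if that has not yet taken place:

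- The statistician sends the interim report, with arms coded, directly to the independent assessor on the board.
- The independent assessor may open the arm key when direction is needed to judge harm. A permanently sealed key would make the harm criterion unworkable.
- Assessors from the participating hospitals keep their review of individual SAEs but do not see by-arm primary-outcome results.
- The PI receives only the recommendation: continue, modify or stop.
- The PI and sites neither produce nor receive by-arm primary-outcome summaries before data lock. This clause is needed because the local PI has access to the database, so rerouting the report would not be enough.

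The cost is a protocol amendment notified to the ethics committees; the trial has three approvals, and enrolment began in January 2016. No extra staff are needed, since the independent assessor is already provided for. The trade-off is that the by-arm primary-outcome review then rests with that one assessor, unless the board has other members uninvolved in the study.

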### Sample size

The lack of information about this topic (temperature during KMC in the specific scenario of head covering) prevented us from obtaining a mathematical estimation of the sample size. Thus, the sample size was arbitrarily defined in order to take into account the enrollment rate of each hospital. According to the number of admissions in each participating hospital, we decided to enroll a total of 300 subjects (150 in the cap group and 150 in the uncovered head group) as follows: 150 at Central Beira Hospital, 90 at St. Luke Wolisso Hospital and 60 at Aber Hospital.

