### Randomization

Eligible infants will be assigned to the KMC + cap or the KMC group in a 1:1 ratio according to a computer-generated, randomized sequence for each participating hospital. The randomized allocation will be concealed in double-enclosed, opaque, sealed, and sequentially numbered envelopes prepared at the University Hospital of Padua.

In the KMC room, the next sequential randomization envelope will be opened only when the attending operator considers the infant to be eligible. The assigned procedure (KMC + cap or KMC group) will be then performed. Cross-over will not be allowed. Analysis will be done as per intention-to-treat. A flow diagram of patient randomization is reported in Fig. 1.

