### Statistical analysis

Analysis will be performed as per intention-to-treat. Continuous data will be expressed as mean and standard deviation (SD) or median and interquartile range (IQR). The effect of the treatment on primary outcome will be assessed using a Poisson model adjusting for hospital and a set of clinically relevant confounders (maternal temperature, environmental temperature, birth weight, postnatal age). The logarithm of the number of measurements during hospital stay will be used as an offset, in order to take into account the different lengths of hospital stay of each participant. The effect of the treatment on the number of episodes of apnea will be assessed using a Poisson model adjusting for hospital and a set of clinically relevant confounders (neonatal and maternal temperatures, environmental temperature, birth weight, postnatal age). The logarithm of the number of measurements during hospital stay will be used as an offset. The effect of the treatment on binary secondary outcome (sepsis and mortality before hospital discharge) will be assessed using a logistic regression model adjusting for hospital and birth weight. The effect of the treatment on continuous secondary outcome (in-hospital growth) will be assessed using a regression model adjusting for hospital. Statistical analysis will be performed using R 3.2.2 software (R Foundation for Statistical Computing, Vienna, Austria) [11]. A *p* value less than 0.05 will be considered statistically significant.

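### The interim criterion for stopping for harm has no direction, so a significant benefit of the cap also meets it; its significance level and its link to the SAE criterion are not fixed either

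*Protocol article*

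**What the plan says.** The Data Safety and Monitoring Board section sets the timing: "An interim analysis will be performed on the primary endpoint and on SAEs from the first 100 enrolled infants". A statistician blind to allocation does the analysis and reports to the PI. The PI discusses it with the monitoring board, and the trial ends if there is harm. The rule then reads: "Criteria for stopping for harm include: a statistically significant difference in the primary outcome between the treatment groups". After a semicolon comes the second criterion: "and a reasonable suspected causal relationship between the intervention and SAEs".

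The Primary outcome measure section defines the outcome as infant temperature staying within 36.5–37.5 °C, so a higher value is the desired result.

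The Statistical analysis section gives the article's only threshold: a p "value less than 0.05 will be considered statistically significant". It states no separate interim level and no adjustment of the final test for the earlier look.

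The Sample size section fixes 300 infants, 150 per arm, and states no power or effect size: "the sample size was arbitrarily defined in order to take into account the enrollment rate of each hospital".

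**The concern.** A harm rule should be triggered by evidence that the intervention makes infants worse off. This one is triggered by any significant difference in an outcome that the cap is expected to improve. Taken as written, the result the trial hopes for at 100 infants is a criterion for ending it under the label of harm.

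Two further points are left open in the same sentence. The first is the level: if the general 0.05 applies at the interim and again at the end, and an interim crossing is reported as a finding, the trial has two unadjusted chances of a false positive. The second is the join between the criteria: the wording does not settle whether a suspected link between the cap and SAEs is enough by itself.

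At stake are an early end at one third of the planned size for a reason the rule mislabels, an overall error above the stated 5%, and a board without an unambiguous instruction.

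**Working it through.** **Inputs.** Interim at 100 infants (Data Safety and Monitoring Board); total 300, which agrees with the site targets 150 + 90 + 60 (Sample size); 1:1 allocation (Randomization); threshold 0.05 (Statistical analysis). Assumptions: the tests are two-sided (the article does not say), and information is proportional to infants. The article states no overall error or power, so there is no figure of its own to reproduce.

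**Set-up.** The information fraction is t = 100/300 = 1/3. The interim and final statistics Z1 and Z2 are bivariate normal with correlation √(1/3) = 0.577. The critical value is 1.960.

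**1. Chance of meeting the criterion because the cap works.** For final power P, the interim mean of Z1 is (1.960 + z_P) × 0.577.
- 80% power: (1.960 + 0.842) × 0.577 = 1.618. In the cap's favour: P(Z > 1.960 − 1.618) = 0.366. Against the cap: P(Z < −1.960 − 1.618) = 0.00017.
- 90% power: (1.960 + 1.282) × 0.577 = 1.872. In the cap's favour: 0.465. Against the cap: 0.00006.

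**2. Overall type I error under no effect, by reading of the rule.**

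| Reading | Error |
|---|---|
| Either direction alone stops the trial and is reported as a finding | 0.0500 at the interim + 0.0383 first crossed at the end = 0.0883 |
| Either direction stops the trial, but no claim is made from the stop | 0.038 |
| Both criteria needed to stop, and the stop is reported as a finding | between 0.05 and 0.0883, depending on how often an SAE link is suspected |
| Only significance against the cap stops the trial (one-sided 0.025): false claims of benefit | 0.025 |
| The same harm-only stop, with the stop itself counted as a rejection | 0.069 |

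A simulation of 2 million draws gives 0.0884 for the first row. If the information fraction were 0.25 to 0.5 instead of 1/3, that row would run from 0.0908 to 0.0831.

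**3. Boundaries that would hold about 5% over two looks at 1/3 and 1 (nominal two-sided p).**
- Haybittle-Peto: 0.001 at the interim. With the final test at 0.05 the total is 0.0505; a final level of 0.0495 gives 0.05.
- O'Brien-Fleming: 0.0007, then 0.0497.
- Equal levels (Pocock type): 0.0277 at both looks.

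**4. The two readings of the join.**
- *Alternatives:* a significant benefit alone meets the harm rule, and the error can reach 8.8%. SAEs can also stop the trial alone.
- *Both required:* a significant benefit alone does not stop the trial, and the error is below 8.8%. Suspected cap-related SAEs then meet the listed rule only with a significant primary difference, which could even be in the cap's favour.

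**The case against.** **A two-directional criterion may be deliberate.** The Background says WHO guidance recommends a hat during KMC, and the control arm goes without one. Ethical considerations says that hypothermic and hyperthermic episodes are monitored in both groups. A clear advantage of the cap could then be seen as harm to uncapped infants. This is a reasonable intention, but the article does not state it. If it is meant, it is a different rule and needs its own name and boundary.

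**Direction can be supplied later.** The statistician is blind, but the PI and the board need not be, and the governing condition is that the trial ends in case of harm. This stands: blinding does not make the rule unworkable. It does mean that direction depends on judgement at that meeting and not on the written criterion.

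**The level may be set elsewhere.** Using 0.05 at the interim is an inference from the general statement in Statistical analysis, and an analysis plan not shown could give another level. This is fair for the level. It does not cure the direction, which the article itself leaves out of a rule it writes down.

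**Stronger readings that the text does not support.** A reader might infer that the plan raises the type I error to 9% outright. It does so only under the first row of the table; no efficacy stop is planned, and a true harm-only stop does not inflate false claims of benefit. A reader might also infer that the word joining the criteria prevents stopping on SAEs alone. The list is introduced as non-exhaustive, and the board reviews all deaths and adverse events in any case, so this is an ambiguity and not a demonstrated block. That inference also needs the opposite reading from the one that produces the benefit-only stop and the full 8.8%, so these consequences cannot be charged together.

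**Conclusion.** The point holds in limited form. The written harm criterion has no direction on an outcome where the cap is expected to help, so a cap that works can meet it. Under assumed effects giving 80% or 90% final power, the probability is about 0.37 or 0.46. These figures illustrate the problem and are not properties of this trial, which states no power. Meeting the criterion ends the trial without more only if the two criteria are alternatives.

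The error figure is an upper case: up to about 8.8%, given a 0.05 two-sided level at both looks, information of one third at the interim, and a stop in either direction, on significance alone, that is reported as a finding. Whether the SAE criterion can act alone is unresolved. The missing direction is the firmest part, because it rests on the article's own wording and on no assumption about power or level. The rule should be settled before the look at 100 infants.

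**What to change.** Reword the rule in the Data Safety and Monitoring Board section.

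- Name the direction of the primary-outcome difference that counts as harm to the cap arm, and state that a difference in favour of the cap is not a harm stop.
- State the interim level for that criterion and how an interim crossing affects the final test and its reporting. The choice of harm threshold is for the board.
- Reconcile the wording so that it says whether the primary-outcome and SAE criteria are alternatives or must both be met.
- If stopping for benefit, or for harm to uncapped infants, is intended, write it as a separate, named rule with an alpha-preserving boundary. Examples are Haybittle-Peto at p < 0.001 (overall error 5.05% with the final test kept at 0.05) or O'Brien-Fleming (0.0007, then 0.0497).

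The cost is protocol wording, with no change in sample size or data collection. If a benefit boundary is added, the final level changes negligibly: 0.0495 or 0.0497 in place of 0.05 to hold exactly 5%.
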